## Abstract

**Introduction:**

Breast cancer is common and women requiring mastectomy will be offered a breast reconstruction if they are surgically suitable candidate. Breast reconstruction can be performed at the same time as the mastectomy (immediate) or delayed to a second operation after cancer treatments. The reconstruction can either use the patients’ own tissue to make the breast (autologous) or use a prosthesis to make the breast in the form of a fixed or expandable volume implant (implant-based breast reconstruction, IBBR). Immediate breast reconstruction on top of the chest wall muscles (prepectoral) is performed worldwide. This operation involves the use of a synthetic or biological mesh placed around the implant under the skin. Increasingly, surgeons are performing this technique without the use of mesh. Both techniques, with and without mesh, have not been compared in a head-to-head randomised controlled trial (RCT); therefore, surgeons and patients do not have high quality data to guide their decision making in this area.

**Methods and analysis:**

UK-based pragmatic multicentre randomised controlled feasibility trial. The primary aim is to determine the feasibility of a definitive RCT comparing the clinical and cost-effectiveness of no-mesh versus mesh-assisted prepectoral breast reconstruction. Secondary objectives will explore patient understanding of mesh and willingness to be randomised within an RCT; determine if it is possible to collect data to inform a future economic analysis on the use of mesh in breast reconstruction and determine the feasibility of measuring breast biomechanics pre-surgery and post breast reconstruction surgery. Total number of patients to be included: 40 (20 per arm).

**Ethics and dissemination:**

This study will be conducted in compliance with the Declaration of Helsinki. Ethical approval has been obtained. Ethics Ref: 23/SC/0302; IRAS Project ID: 301 423. The results of this study will be published in a peer-reviewed medical journal, independent of the results, following the Consolidated Standards of Reporting Trials standards for RCTs.

**Trial registration numbers:**

NCT06112977; ISRCTN17470747.

STRENGTHS AND LIMITATIONS OF THIS STUDYThis is a pragmatic well-designed feasibility randomised controlled trial (RCT) which aims to determine if a future RCT is possible to run to determine the role of mesh in breast reconstruction.A mixed-methods qualitative and quantitative approach with patient public involvement input throughout the trial processes has been designed to understand all stakeholders’ views. Importantly, participant views on the acceptability of blinding and surgeon views on randomisation will be collected as these may be key barriers to future trial recruitment.The data from a feasibility RCT may support the safety and acceptability of the intervention; however, no statistically significant differences can be determined between the two groups of data.The study is limited to short-term surgical outcomes, and longer-term surgical and oncological outcome measures will be collected pending further ethical approval and funding.

## Introduction

### Background and rationale

 Breast cancer affects one in eight women.^1^ It impacts the lives of 55 000 women per year in the UK and over 2 million worldwide; 80% will require surgery. Of these, approximately 40% require a therapeutic mastectomy to treat their cancer and most will be offered breast reconstruction.^2^ Patients with genetic mutations predisposing to breast cancer may choose prophylactic bilateral mastectomy and reconstruction also.^3^ Women choosing to reconstruct their breast at the same operation as their mastectomy (immediate reconstruction) can choose to either use their own tissue (autologous) or a prosthesis (implant or expandable implant) to make the breast shape.

The modern technique for immediate implant-based breast reconstruction (IBBR) involves an implant wrapped in mesh to form the breast following the mastectomy. The implant is placed in front of the pectoralis chest wall muscle (prepectoral). Prepectoral reconstruction was developed in 2015 to avoid the morbidity of raising the pectoralis muscle to cover the implant which resulted in upper body weakness and animation deformity associated with the older technique (submuscular).^4^

Mesh was introduced as a substitute to using the pectoralis muscle to cover the implant in the reconstruction. Uncertainty exists regarding the benefits of mesh; however, it is used in the majority of prepectoral reconstructions in the UK.^5^ Reported benefits from mesh are improved cosmesis and providing support and cover to the implant on the chest wall. There is an increasing public awareness of mesh in surgical operations and complications with mesh use.^6^ Surgeons can safely perform the procedure without the use of mesh, and this technique has become more popular in the past few years.^7^

National data indicate that 36% of women will experience complications requiring unplanned interventions following implant-based reconstruction.^8^ Meta-analyses on published data report mesh may increase complication rates in breast reconstruction; however, data in this field are limited by high levels of heterogeneity and retrospective case series.^9^ Cancer patients are on tight treatment pathways; complications from surgery can delay adjuvant treatments, for example, chemotherapy and radiotherapy, potentially adversely impacting long-term oncological outcomes and patient well-being.^10^

There is a need for high-quality evidence in this field at an international level to inform clinical and health policy decisions about the use of mesh in breast reconstruction and facilitate shared surgeon-patient decision making in the breast clinic.

## Objectives

The main purpose of this trial is to determine the feasibility of conducting a single-blinded randomised controlled trial (RCT) comparing no-mesh to mesh-assisted prepectoral IBBR. Feasibility data on the trial will be collected throughout the trial and assessed on completion of the recruitment period. Specifically, the proportion of patients eligible, proportion of patients consented and randomised, proportion of patients lost to follow-up or withdrawn from the study will be quantified and used to inform the assessment of feasibility of a corresponding definitive (‘main’) trial. Patient and clinical equipoise to the two intervention arms and willingness to take part in the trial will also be assessed through a qualitative component involving interviews. The trial will collect data on clinical and patient outcomes to inform a future cost-effectiveness decision model structure for IBBR. Completeness of data per participant at 3 months postoperatively and clinical outcome measures will be collected to inform a future RCT sample size calculation. Traffic light criteria will be applied at the end of the feasibility trial to determine progression to the definitive RCT.

Two optional substudies will be offered to patients:

A qualitative interview with a trial researcher to discuss their views on mesh in IBBR, trial design and barriers to research participation. This interview is open to both women who would like to participate in the trial and those who decide not to take part.

Participants who consented to the main trial will be offered the opportunity to take part in a substudy to determine the feasibility of assessing breast biomechanics pre-IBBR and post-IBBR.

## Methods and analysis

### Patient and public involvement

Patient advocates are members of the trial management committee and trial steering committee and have been involved in all aspects of trial design and conduct. Two members are coauthors on this publication. The design of this trial places patient views at the centre of the study through qualitative interviewing and inclusion of patient ranking of outcome measures within the trial to understand what issues matter most to patients undergoing this breast reconstruction surgery. The results of this study will be broadly broadcast to patients involved in the study via the trial newsletter and general public via publication of results in a peer-reviewed scientific journal, conference presentation and social media.

### Trial design and setting

This is a prospective multicentre parallel 2-armed participant-blinded, randomised controlled feasibility trial will compare two surgical techniques for prepectoral IBBR: no-mesh versus mesh-assisted breast reconstruction. The two interventions will be allocated in a 1:1 random allocation at the time of surgery. We will recruit a total of 40 patients from breast reconstruction surgery centres across the UK. The prepectoral breast reconstruction will be performed according to the surgeon’s usual standard of care; the only difference between the two arms will be the placement of mesh or not in the breast reconstruction. Participants will be blinded to their allocation until 90 days postoperatively and will be unblinded after completion of their 90 day postoperative quality of life (QoL questionnaire (figure 1 shows the trial design). The study duration is planned for 12 months with 90 days follow-up for each participant.

**Figure 1 F1:**
[figure not shown]
Trial flow chart.

### Eligibility criteria

Women with a diagnosis of breast cancer or a gene mutation predisposing to breast cancer undergoing immediate pre-pectoral IBBR will be eligible to participate in the trial. Women must be over 18 years of age, willing and able to give informed consent and able to comply with all trial requirements. Patients are unable to enter the trial if the participant becomes pregnant or is planning pregnancy or breastfeeding; refuses to enter the trial or is undergoing delayed breast reconstruction post simple mastectomy. Both unilateral and bilateral breast reconstructions are included in the trial. Randomisation will take place at the patient level; therefore, a bilateral case will have the same allocation across both reconstructions. Each patient will be informed that participation is voluntary and withdrawal at any point within the trial is supported and would not affect ongoing medical care.

### Intervention and comparator

#### Main trial

The local principal investigator will confirm a patient’s eligibility to participate in the trial having identified patients from their multidisciplinary team meetings and oncoplastic clinics. The trial will be offered to the patient and a written patient information sheet will be given prior to consent. After written informed consent has been obtained by the local principal investigator, patient baseline data will be collected using case report forms (CRFs) accessed via the online database RedCap. CRFs will include collection of routine clinical data including patient and tumour characteristics, comorbidity and cancer treatments and progress through the treatment pathway. This information will be collected as required to describe the cohort and assess the representativeness of those recruited within the study to the general breast cancer and risk-reduction population.

Routine baseline medical photographs and a preoperative patient QoL questionnaire will be sent for completion. This includes the BREAST-Q and EQ5D QoL questionnaires and patient ranking of clinical outcome measures from least important to most important to them which are emailed to participants. QoL questionnaire data will form part of the economic modelling for the two interventions. Preoperative and postoperative photographs will be anonymised and assessed via a blinded patient and professional panel for breast aesthetics between the two groups who will view the images pre- and post-operatively and mark them out of 5 on a Likert scale for cosmesis (RR3).

### Outcomes

The primary endpoint of this study is the feasibility criteria to progress to a future main RCT comparing no mesh to mesh assisted prepectoral IBBR. The main limiting factor for surgical trials is recruitment. A progression dashboard with red/amber/green thresholds is proposed to evaluate the success of the feasibility trial. Achieving all green targets means proceeding to full proof-of-concept is feasible, whereas achieving all red targets would almost certainly indicate that a full proof-of-concept is not feasible. A mixture of green/amber/red thresholds will result in restrategising: recruitment and/or retention strategies will be reconsidered. The primary outcome to be measured for a future RCT will be determined through patient and surgeon ranking of clinical outcome measures and qualitative interviewing of patients to understand what matters the most to patients and surgeons in IBBR.

### Data collection methods

Intraoperative data will be collected including details on the mastectomy technique and volume, the type and volume of prosthesis (±mesh) used in the operation, mastectomy weight, use of sutures, drains and antibiotics.

Preoperative, perioperative and postoperative care will be standard NHS care as per local practice including standard surgical outpatient follow-up at 14 days, 30 days and 90 days. Clinical outcome data will be collected at the same time points as NHS care. Clinical data collected includes clinical history, clinical postoperative complications and patient access to healthcare outside of the tertiary hospital setting via patient weekly online diaries.

Patients will be contacted at 90 days to complete an online (or paper) QoL post-operative questionnaire (in rare cases by telephone). Following completion of the 90-day QoL questionnaire, the patient will be unblinded to their allocation. Standard postoperative oncoplastic photographs will be collected at 90 days to assess breast aesthetics. Patients can report complications or additional healthcare visits to the research team via their weekly online diary. Serious adverse events will be recorded and reported if unexpected and related. Feasibility outcome data will be collected alongside clinical outcome data. Data will be collected from participants via questionnaires and CRFs. Paper questionnaires (where used) will be returned to the central trial office in Oxford via post using a preaddressed freepost envelope. Electronic questionnaires will feed directly into an online secure database—the study’s dedicated instance of REDCap (figure 2 shows the schedule of events).

**Figure 2 F2:**
[figure not shown]
Schedule of procedures. CRF, case report form; D, day; OPA, outpatient appointment; Preop, preoperative.

####  Optional

Patients, when offered participation in the trial, will be in parallel offered to participate in the substudy looking to identify patient views on mesh in breast reconstruction, the design of the trial and barriers to participation in research. A patient information sheet and consent form for the qualitative interview (previously approved ethics reference: Narratives of health experience insights for https://hexi.ox.ac.uk and www.youthhealthtalk.org. b NRES Committee South Central - Berkshire 122/SC/0495. IRAS ID 112111). This is in the form of a 1-hour virtual (or face-to-face) qualitative interview with the trial research team. Patients can participate in this study regardless of their decision to take part in the main study. Participants in this substudy will be compensated for their time with a gift voucher. Deidentified transcripts will be analysed using thematic analysis, guided by a modified grounded iterative theory approach, allowing early interviews to enrich data collection in later interviews. Patients will be interviewed until analytic categories are richly covered with no further emergent themes. Three levels of coding will be used to develop conceptual analysis.Patients who decide to consent to participate in the main trial will be offered the opportunity to take part in the substudy determining the feasibility of collecting breast biomechanic data presurgery and post breast reconstruction surgery. Patients will be approached preoperatively in the outpatient setting by the consenting surgeon. Trial information and trial consent for biomechanics will be supplied to patients at this visit. Participants who wish to participate will be invited to attend a preoperative and postoperative visit (at 90 days) to the biomechanics laboratory for data collection in addition to their standard NHS care visits to their hospital. Patients will need to be able to travel to the biomechanics data collection site at the University of Portsmouth. Patients will be compensated for their travel costs to the biomechanics laboratory. Participants who do consent to biomechanical data collection will have an appointment made at the University of Portsmouth breast biomechanics centre. Electronic sticker sensors (Liberty MicroSensor, Polhemus, Vermont, USA; CE Marked) will be placed onto the patient’s chest wall and breast and the patient will be asked to stand, walk slowly and walk quickly with the sensors collecting data on breast volume, shape and position statically, plus full body and breast kinematics dynamically, as well as perceptual feedback related to their breasts. Breast volume, shape and position will also be assessed statically using 3D scanning (Artec Eva 3D, Luxembourg; CE Marked). Three-dimensional motion of the body and breast will be tracked using electromagnetic sensors and data derived to calculate breast motion relative to the torso (six df). All biometric data collected is anonymous and linked to the participant study ID. Biomechanical data will be analysed by the research team. Participants in this substudy will be offered an optional questionnaire to record their views on this aspect of the trial. All participants will be given a complimentary bespoke postoperative bra according to their breast biomechanical data.

### Harms

The safety reporting window for the trial will be from the time of consent and will end at 90 days postoperatively at the end of the trial. Following the last feasibility assessment at 90 days, patients will be followed up clinically by their healthcare team as part of routine clinical NHS (National Health Service) care. Investigators’ follow-up of adverse events will be until event resolution or stabilisation. An adverse event is defined as any untoward medical occurrence in a participant to whom the intervention has been administered, including occurrences which are not necessarily caused by or related to that intervention. A serious adverse event (SAE) is defined as any untoward medical occurrence that: results in death; is life-threatening; requires inpatient hospitalisation or prolongation of existing hospitalisation; results in persistent or significant disability/incapacity; is otherwise considered medically significant by the investigator. The patient will be unblinded if they suffer a severe unexpected adverse event and knowledge of allocation is required. The PI will be able to access the operation note for the patient on their trial site electronic records and assess if a mesh was used or not. If it is not clear on the operation note, the trial statistician will access the randomisation schedule to code-break for the specific participant. The CI will remain blinded to allocation.

Only events considered related to the intervention and considered serious are recorded as an SAE. This includes any assessment results outside of normal parameters.

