#### Reporting of SAEs

All side effects collected as outcomes in the CRF that also meet the definition of serious will need to be reported as an SAE during the trial’s safety reporting window. The safety reporting window is from the day of surgery (intervention) until the 90 day postoperative outpatient review at the end of the trial. Reporting must be within 24 hours of the site being aware of the SAE. Once a SAE is entered in the RedCap trial database, this automatically triggers a notification to the clinical trial unit.

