### Blinding

Due to the nature of the intervention, it is not possible to blind the surgeons for the purpose of the trial. Participants will be blinded to their allocation. On withdrawal or at the end of the trial, the patient will be informed of their allocation at 90 days postoperatively. Unblinding will occur after completion of the 90 day postoperative QoL questionnaire to reduce bias in its completion. Data will be collected on the administrative processes of randomisation, allocation concealment and the effectiveness of the blinding strategy of the patient to the allocation. Assessment of cosmesis between the two arms will be via a blinded panel of surgeons and patient public representatives using an established cosmetic scoring system.^11^ All questionnaires used in the trial (EQ5D and BREAST-Q) are validated questionnaires. Trial data analysis will be blinded to allocation to reduce bias in data interpretation.

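### The article gives conflicting rules for which serious adverse events are recorded and reported, and two start dates for the safety window

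*Protocol article*

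**What the plan says.** The protocol article deals with serious events in three sections.

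- **Harms, definitions.** The adverse event definition covers untoward occurrences "including occurrences which are not necessarily caused by or related to that intervention". For seriousness it says "A serious adverse event (SAE) is defined as any untoward medical occurrence that" meets one of the listed criteria, among them inpatient hospitalisation. Neither definition has a relatedness condition.
- **Harms, closing paragraph.** "Only events considered related to the intervention and considered serious are recorded as an SAE".
- **Data collection methods.** "Serious adverse events will be recorded and reported if unexpected and related".
- **Reporting of SAEs.** Here the rule is "All side effects collected as outcomes in the CRF that also meet the definition of serious will need to be reported as an SAE", within 24 hours of the site becoming aware. Entry of an SAE in the trial database automatically notifies the trials unit.

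The window is also stated twice. Harms says "The safety reporting window for the trial will be from the time of consent"; Reporting of SAEs says "The safety reporting window is from the day of surgery (intervention".

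On blinding, the Blinding section says "it is not possible to blind the surgeons for the purpose of the trial". Harms adds that the local principal investigator can consult the operation note when a code-break is needed and that the chief investigator stays blinded. No section says who judges relatedness.

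**The concern.** A site needs one rule for deciding whether to open an SAE form. Here it could follow any of three and be compliant with one section while breaching another. Sites that follow different sections would produce SAE data that cannot be pooled or compared.

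The narrower rules also apply relatedness at the point of recording, where it decides whether an SAE entry exists. Relatedness and expectedness usually decide only how fast, and to whom, a recorded event is passed on. Because the notification depends on an SAE being entered, an event filtered out raises no alert. The section on the data and trial monitoring committee states that there is no formal data monitoring committee, and the independent steering committee meets every six months, so the alert carries some weight.

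Finally, relatedness is a judgement, and the people most likely to make it at a site may know the allocation. The article expects the data to bear on the safety of the intervention and plans descriptive summaries by treatment group. Both call for an SAE record kept in the same way in each arm.

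**Working it through.** No figure in the article is at stake, so the check is to take kinds of event that all meet the seriousness definition and ask what each statement does with them. For Data collection methods, the table takes both conditions as applying to recording.

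| Serious event | Harms definition | Harms closing rule | Data collection methods | Reporting of SAEs |
|---|---|---|---|---|
| Related, unexpected, a CRF outcome | SAE | recorded | recorded and reported | reported |
| Related, expected, a CRF outcome | SAE | recorded | not recorded | reported |
| Judged unrelated, a CRF outcome | SAE | not recorded | not recorded | reported, unless *side effect* is taken to imply causation |
| Related, expected, not a CRF outcome | SAE | recorded | not recorded | not covered |
| Judged unrelated, not a CRF outcome | SAE | not recorded | not recorded | not covered |

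1. **Agreement.** All four columns agree only in the first row.
2. **The central example.** A readmission for implant infection meets the hospitalisation criterion, and implant infection is one of the rates that the Sample size section says will be calculated. If a site regards it as expected, it falls in the second row (or in the third, if judged unrelated): reportable within 24 hours under one section, outside the SAE record under another.
3. **Events with no other route.** In the last row, an event is an SAE by definition, yet no operating rule brings it into the SAE record. As it is not a CRF outcome either, it might not be captured at all.
4. **The window.** A serious event between consent and surgery is inside the window in Harms and outside it in Reporting of SAEs. The adverse event definition in Harms covers only participants who have received the intervention, which fits the later start and not the earlier one stated in the same section.
5. **Could the filter act by arm?** Three facts make it possible: surgeons are unblinded, sites report, and relatedness is to the *intervention*, whose meaning shifts. Reporting of SAEs glosses it as the surgery, which both arms receive. Trial design and setting uses it for the two allocated techniques, which differ only by mesh. On the first meaning attribution should be similar in both arms; on the second it need not be.
6. **Size.** The article gives no SAE rate and no share of events judged related, so neither the number of events left out nor any difference between arms can be calculated.

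**The case against.** **Complications are captured elsewhere.** Data collection methods collects postoperative complications at 14, 30 and 90 days with no relatedness filter, and adds weekly diaries from participants who are blinded until day 90. Implant loss, infection and seroma rates are calculated as outcomes. This stands. A reader might infer that filtered events are gone for good; the documents do not support that. What the SAE rules put at risk is the SAE label, the alert, and any serious event that is not a CRF outcome.

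**Data collection methods can be read more kindly:** all SAEs recorded, with onward reporting if unexpected and related. The wording allows this. It would remove that section's filter on recording but leave the conflict between the Harms closing rule, the Harms definition and Reporting of SAEs.

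**Biased attribution is inferred.** No section names the assessor. Nor is it certain that mesh would attract more blame: the background lists implant support and cover among its reported benefits, so its absence could be blamed too. This stands, and the direction of any bias should not be asserted.

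**Putting numbers on it.** A reader might take the 36% quoted in the background, apply it to 20 per arm (0.36 × 20 = 7.2 events), and assume unequal shares judged related. With 100% in one arm and 80% in the other, 7.2 and 5.8 would be recorded; with 100% and 60%, 7.2 and 4.3; with equal shares there is no gap. The shares are assumptions and the gap only restates them. The 36% refers to complications needing unplanned intervention, not to SAEs, and many of these would be collected as complications anyway. It therefore does not show that most such events would go unrecorded.

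**Nothing primary depends on SAE counts.** The primary endpoint is feasibility, no formal comparison is planned, and central monitoring, monthly management meetings and the steering committee also review safety. This limits the consequence to oversight and descriptive safety summaries. It does not make the instructions consistent.

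**The article is condensed.** That can explain missing detail, but not positive statements that disagree.

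**Conclusion.** The point holds as a contradiction in the safety rules. Three sections give three different conditions for an SAE to be recorded or reported, one of them against the definition in its own section, and the window has two start dates. Following the narrower rules as written keeps some serious events out of the SAE record and its alert, and leaves those that are not CRF outcomes possibly uncaptured.

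A difference by arm is possible. It rests on two assumptions that the article does not settle: that an unblinded person at the site judges relatedness, and that the intervention means the allocated technique. Its size and direction are unknown. The feasibility endpoint is unaffected.

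**What to change.** Reconcile Harms, Data collection methods and Reporting of SAEs so that they state:

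- **One recording rule.** Every event meeting the seriousness definition in Harms is recorded as an SAE in both arms, whatever its relatedness or expectedness. The sentences that make recording conditional on these are removed.
- **One reporting rule.** Relatedness and expectedness are used only to decide onward expedited reporting.
- **One window,** with a single start, matched to the adverse event definition.
- **A definition of the intervention for causality,** saying whether it means the reconstruction operation or the allocated technique.
- **The causality assessor,** named by role, with that person's blinding status.
- **A descriptive table of all serious events by arm,** with relatedness as a recorded attribute.

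The cost is an amendment to the protocol and CRF guidance, and a few more SAE forms in a trial of 40. Because recruitment began in March 2024, complication records already held should be checked once against the agreed rule.
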